### Intervention description {11a}

#### Intervention design

The intervention consists of a structured, individualized, dyadic, collaborative approach, identifying and addressing the needs of both the PlwD and the informal caregiver. Family Care Specialists (qualified nurses) identify the care and support needs of the dyad using a tablet-based intervention management system (IMS).

In general, the intervention consists of four key components:i.Initial needs assessment at the memory clinic, followed by a home visit with a comprehensive initial resource and need assessment of the dyads in their current home-living situation. In these assessments, comprehensive information regarding the medical, psychological, pharmaceutical, social and nursing situation is collected to identify the individual resources and unmet needs of both the caregiver and the PlwD. The information collected informs the subsequent selection of intervention tasks, which are then tailored by the Family Care Specialist to the dyad’s context and preferences.ii.Generation of an individual intervention task list based on the identified unmet medical, psychosocial, and care-related needs. While the system does not explicitly assess personal life history, the Family Care Specialist evaluates the suitability of the suggested tasks for the dyad and adapts them as necessary to match the dyad’s capabilities, preferences, and context.iii.Collaborative completion of the task list by the Family Care Specialist in close cooperation with the treating general practitioner of the caregiver and the PlwD and other healthcare and social services providers involved in the care for either the caregiver, or the PlwD, or both during the 12-month intervention period. Tasks are reviewed and adjusted collaboratively with the dyad to ensure they are feasible and appropriate. The Family Care Specialist may also add tasks not predefined in the IMS if these better align with the dyad’s needs and preferences.iv.Access to a mobile health app for caregivers for digital support, caregiver burden monitoring, and connection to the Care Specialist and the memory clinic at any time, enabling timely response as well as identification of emerging unmet needs and additional intervention tasks.

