#### Qualitative data

In addition to the quantitative analyses, we will conduct guided interviews with experts who are involved in the care process (e.g., physicians in specialized care) to assess facilitators, barriers, acceptance, usability and feasibility of the intervention. In addition, the usability of the Mobile Health App and the Intervention Management System will be evaluated. Interviews will be conducted with *n* = 8 participating dyads, *n* = 8 Family Care Specialists, and *n* = 3 physicians from participating memory clinics. The qualitative data will be evaluated using content analyses by Mayring [31].

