### Sample size {14}

Sample size was exclusively calculated based on a dichotomized threshold (≥ 12 months) of the PTS. Based on data from previous studies, 60% of informal caregivers of community-dwelling PlwD initially expressed their confidence in maintaining the informal care provision and the current care arrangements for at least 12 months. However, 10.5% of patients died and only 23% of the initial sample maintained this view one year later [21]. We, therefore, hypothesize that the intervention will increase this proportion to 35%, corresponding to an effect size of 0.25. Assuming a 1:1 randomization, statistical power of 80%, and a significance level of *α* = 0.05, a sample size of 224 dyads per group is required to detect a statistically significant effect based on a chi^2^ test. Considering an additional drop-out rate of 17.5%, summing up to 28% including death (in line with previously conducted study [43]), the target sample size increases to 272 dyads per group, resulting in a total of 544 dyads (1088 participants: 544 PlwD and 544 caregivers).

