## Statistical methods

### Statistical methods for primary and secondary outcomes {20a}

All data analyses will be conducted using pseudonymized datasets. Initially, all outcome variables will be subject to descriptive statistical analyses. At baseline, the intervention and control groups will be compared regarding significant differences, serving as a randomization check. If notable differences are identified, all subsequent analyses will be adjusted for the respective factors. After completing the assessment, we will conduct a drop-out analysis using multivariate logistic regression to evaluate any systematic differences between included and excluded patients.

For the primary outcome, an ordinal logistic regression (proportional odds model) will be used to analyze the full six-category ordinal scale PTS. The intervention effect on the secondary outcomes will be evaluated using multivariate linear and logistic regression models, adjusted for age, sex, and living situation (alone vs. together with the caregiver), and including random effects for the respective memory clinic to account for clustering. The different study sites will be treated as clusters in these analyses. The analyses will be done on intention-to-treat (base case analysis) and per-protocol analyses (sensitivity analysis).

For the health-economic evaluation, the incremental cost-effectiveness ratio (ICER) will be calculated by comparing the additional cost per QALY gained through the intervention. Nonparametric bootstrapping resampling will be used to account for sample uncertainty in the ICER estimates. Various willingness-to-pay thresholds will be applied to determine probabilities of cost-effectiveness.

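### Family Care Specialists act in one arm only, but only the study site is named as a cluster; if specialists differ, the treatment effect's standard error is too small for the generalisation the trial intends

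*Protocol article*

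**What the plan says.** The section Statistical methods for primary and secondary outcomes {20a} analyses the primary outcome, the six-category PTS, with a proportional odds model. That sentence has no cluster term. The next sentence, on the secondary outcomes, adds random effects for the memory clinic. Then follows "The different study sites will be treated as clusters in these analyses". It can be read as covering all the models or only the secondary ones. No section mentions the specialist as a source of correlation.

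Other sections describe the structure of the trial:
- Intervention design: the specialist judges whether suggested tasks suit the dyad and adapts them. In addition, "The Family Care Specialist may also add tasks not predefined in the IMS if these better align with the dyad’s needs and preferences".
- Explanation for the choice of comparators {6b}: controls receive usual care, so no specialist acts on them.
- Confidentiality {27}: each specialist is tied to one memory clinic.
- Sequence generation {16a}: dyads are randomised in blocks within clinic, so every clinic holds both arms.
- Sample size {14}: a plain chi-square calculation without a design effect.
- Discussion: the results are expected to carry over to memory clinics throughout Germany and to support transition to standard care.

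**The concern.** Dyads looked after by the same specialist for a year share that person's skill and choices, so their outcomes may be correlated. This correlation exists only in the intervention arm. A clinic effect common to both arms removes differences between clinics in the level of the outcome. It does not remove differences between specialists in what the intervention achieves, not even with exactly one specialist per clinic, because that clinic's controls are untouched by the specialist.

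What is at stake is the precision claimed for the treatment effect on PTS, NPI and ZBI. If specialists differ and this is ignored, the confidence interval is too narrow for a statement about the care model in other hands. The trial would also not report how far its result depends on who delivered the care.

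**Working it through.** **The plan's own figure.** Inputs from Sample size {14}: in the control arm "only 23% of the initial sample maintained this view one year later"; "the intervention will increase this proportion to 35%, corresponding to an effect size of 0.25"; 80% power; "a significance level of *α* = 0.05", taken as two-sided. With a mean proportion of 0.29:

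n = [1.96·√(2·0.29·0.71) + 0.8416·√(0.23·0.77 + 0.35·0.65)]² / 0.12² = (1.2578 + 0.5353)² / 0.0144 = 223.3, so 224 per group.

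With 17.5% drop-out, 224/0.825 = 271.5, so 272. Both stated figures reproduce under independent observations, which confirms that no clustering is allowed for.

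**Adding specialists in one arm.** Two inputs are not in the article and are assumed:
- Number of specialists, k: 5, 8 or 20. The only figures at hand are five clinics and the 8 specialists to be interviewed (Qualitative data).
- Specialist ICC: 0.01, 0.02 or 0.05.

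With 224 analysed dyads per arm and equal caseloads:
- caseload m = 224/k
- design effect in the intervention arm, DE = 1 + (m − 1)·ICC; in the control arm it is 1
- true over naive standard error, R = √[(1 + DE)/2]
- actual two-sided error of a nominal 5% test = 2·[1 − Φ(1.96/R)]
- power of a test that uses the correct standard error = Φ[(0.12 − 1.96·SE0)/SE1], where SE0 = √[0.29·0.71·(1 + DE)/224] and SE1 = √[(0.23·0.77 + 0.35·0.65·DE)/224]

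Example, k = 8 and ICC 0.02: m = 28, DE = 1 + 27·0.02 = 1.54, R = √1.27 = 1.127, and 1.96/1.127 = 1.739 gives an error of 8.2%.

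| k | m | ICC | DE | R | Type I error | Power |
|---|---|---|---|---|---|---|
| 5 | 44.8 | 0.01 | 1.44 | 1.10 | 7.6% | 72% |
| 5 | 44.8 | 0.02 | 1.88 | 1.20 | 10.2% | 64% |
| 5 | 44.8 | 0.05 | 3.19 | 1.45 | 17.6% | 49% |
| 8 | 28 | 0.01 | 1.27 | 1.07 | 6.6% | 75% |
| 8 | 28 | 0.02 | 1.54 | 1.13 | 8.2% | 70% |
| 8 | 28 | 0.05 | 2.35 | 1.29 | 13.0% | 58% |
| 20 | 11.2 | 0.01 | 1.10 | 1.03 | 5.6% | 78% |
| 20 | 11.2 | 0.02 | 1.20 | 1.05 | 6.2% | 76% |
| 20 | 11.2 | 0.05 | 1.51 | 1.12 | 8.0% | 70% |

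At ICC 0, DE = R = 1 and nothing changes.

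**Does adjusting for site cure it?** A simulation used a continuous outcome, five sites entered as fixed effects in place of the random clinic effect, specialists nested in sites, a specialist effect in the intervention arm only, and 20,000 runs per setting. For ICC 0.01, 0.02 and 0.05 it gave type I errors of 6.7%, 8.7% and 14.1% with 8 specialists, and 5.7%, 6.2% and 8.1% with 20. At ICC 0 the error was about 5%. Site adjustment therefore leaves the inflation in place. For the ordinal PTS model these figures are an approximation.

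**The case against.** **The headline size rests on assumed inputs.** This stands. The 8 specialists are an interview sample, not a headcount, and no ICC is given. A reader might infer that the trial has few specialists and that its standard errors are simply wrong. The article supports neither. With 20 specialists and ICC 0.01 the effect is minor.

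**Delivery is partly standardised.** This also stands. The intervention management system proposes tasks by predefined rules, contact frequency follows PTS and ZBI thresholds, and tasks are worked through with the dyad, general practitioners and other providers. A reader might picture specialists discarding tasks at will, but the article speaks of adapting and adding, with adjustments made together with the dyad. All this may keep the ICC low, though nothing shows that it is zero.

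**The false-positive figure needs a particular null.** Correct. If the intervention does nothing for anyone, specialists cannot differ in its effect and this mechanism inflates nothing. The inflation applies when the effect averages zero over a wider population of specialists but varies among them. Inference restricted to the specialists employed would be a legitimate choice; the Discussion, however, claims the wider one. The interval is also affected at any true effect: with 8 specialists, actual coverage would be 100% minus the error above, about 93.4% to 87%.

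**The random-effects structure may be settled in the analysis plan.** Partly. The article does not say that the clinic effect is an intercept only, and a treatment-by-clinic term would capture part of the variation. But the article is not silent on clustering: it names the level, and that level is the site.

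**The primary model has no cluster term.** A reader might infer this from its sentence. The text is ambiguous rather than clear, so the right request is clarification.

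**A specialist variance is hard to estimate with few specialists.** This stands, and it argues against making the partially nested model the main analysis.

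**Conclusion.** The point holds in conditional form. The plan names only the study site as a cluster, while a source of correlation confined to the intervention arm goes unmodelled, and a clinic effect shared by both arms does not remove it. For any specialist ICC above 0 the standard error is too small for inference beyond the specialists employed, which is the inference the Discussion draws.

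The size is unknown. Under the assumptions shown it runs from negligible (20 specialists, ICC 0.01: standard error ratio about 1.03) to serious (8 specialists, ICC 0.05: ratio 1.29 and type I error about 13%; worse with 5). The article does not establish that the standard errors are in fact too small or that the error rate in fact exceeds 5%. This is a worthwhile, cheap improvement and does not require a new main model.

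**What to change.** - State the number of Family Care Specialists and record the responsible one for every intervention dyad. Recruitment began in January 2026, so complete this for dyads already enrolled.
- Pre-specify, for PTS, NPI and ZBI, a sensitivity analysis with a partially nested specialist random effect: intervention arm only, each control dyad its own unit, clinic retained. If there is one specialist per clinic, use a treatment-by-clinic random effect instead. Apply a small-sample correction where one is available for the model.
- Report the between-specialist variance beside the main result.
- State in section {20a} that clinic is accounted for in the primary PTS model, and how.

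The cost is one variable and a few lines of analysis wording. The downside is a wider interval if specialists differ, and an imprecise variance estimate if they are few. The power column shows what an honest test could lose at the planned size, which is a reason to keep this as a sensitivity analysis and to read it with the number of specialists in view.

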### Outcomes {12}

Primary and secondary outcomes will be assessed at baseline and 12 months after baseline by qualified study nurses not knowing the group assignment via face-to-face interviews and by caregiver self-assessments at the participating memory clinics, allowing for blinded assessment. Furthermore, baseline assessments will be conducted before randomizing dyads to the intervention or control group, also supporting blinding.

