#### Health economic evaluation

For the health economic evaluation, we will measure the dyads’ health-related quality of life by applying the EQ-5D-5L [39] and the EQ-HWB-S [40] as patient and caregiver self-ratings within interviews. The EQ-5D-5L is a widely used, standardized generic instrument that measures the respondent’s health-related quality of life in five dimensions. Responses can be summarized in a health profile that is associated with a health utility index, ranging from zero (death) to one (full health). In combination with the patient’s and caregiver’s life expectancy, the index can be used to calculate quality-adjusted life years (QALYs) for both the patient and the caregiver. The EQ-HWB-9 (EQ Health and Wellbeing short version) is a new generic instrument to measure health and well-being for social care recipients and caregivers and captures a range of health and broader quality of life aspects in seven dimensions.

Healthcare resource use, which is also required for the health economic evaluation, is captured using the Questionnaire for Health-Related Resource Use in an Elderly Population (FIMA) [41] and the Resource Utilization in Dementia Questionnaire (RUD) [42]. These instruments assess the use of medical, formal, and informal care resources, enabling cost calculation from both a payer’s and a societal perspective.

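### The ICER is adjusted for baseline EQ-5D-5L utility only if a baseline check flags a difference, which leaves avoidable random error in the incremental QALY

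*Protocol article*

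**What the plan says.** The section on statistical methods for primary and secondary outcomes {20a} treats the economic evaluation in its own short paragraph. There "the incremental cost-effectiveness ratio (ICER) will be calculated by comparing the additional cost per QALY gained through the intervention", and "Nonparametric bootstrapping resampling will be used to account for sample uncertainty in the ICER estimates". Probabilities of cost-effectiveness are then read off at several willingness-to-pay thresholds. No covariates are named.

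The paragraph before it does name covariates for the secondary-outcome regressions: "adjusted for age, sex, and living situation (alone vs. together with the caregiver), and including random effects for the respective memory clinic". The baseline value of the outcome is not among them. Earlier in the same section, the arms are to be compared for significant differences at baseline, and "If notable differences are identified, all subsequent analyses will be adjusted for the respective factors". No level or definition of notable is given. The section on additional analyses {20b} repeats a rule of this kind and gives age, gender and dementia severity as examples.

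On timing, Outcomes {12} says: "Primary and secondary outcomes will be assessed at baseline and 12 months after baseline". On QALYs, the health economic evaluation section says that, together with life expectancy, "the index can be used to calculate quality-adjusted life years (QALYs) for both the patient and the caregiver". It gives no formula.

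**The concern.** With utility measured at two visits a year apart, the usual within-trial QALY is the average of the two values. Baseline utility is then a component of the outcome as well as a predictor of it. If one arm happens to start with higher utility, half of that difference is counted directly as QALYs gained, and correlation between the visits adds more through the month-12 value. The bootstrap resamples the observed dyads, so it reflects this variation in the width of the interval but does not remove it from the estimate.

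The stated rule adjusts only when a check flags a difference. Most chance differences fall below any such flag and stay in the result. At stake is the precision of a result that the Discussion wants to use in support of transition to standard care. Making the choice of adjustment depend on the observed baseline data also leaves room for judgement after the data are seen.

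**Working it through.** **Plan's own figure.** The article gives no precision for QALYs or the ICER. Its only sample-size figure is for the dichotomised Perseverance Time Scale, and it reproduces. With 23% vs 35%, two-sided 5%, 80% power and pooled variance: [1.960 × √(2 × 0.29 × 0.71) + 0.842 × √(0.23 × 0.77 + 0.35 × 0.65)]² / 0.12² = 223.3, so 224 per group. Then 224 / (1 − 0.175) = 271.5, so 272 per group and 544 in total. I use n = 224 per arm below.

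**Assumptions not in the article.** Utility SD s = 0.25 at both visits; correlation r between baseline and month 12 of 0.3, 0.5 or 0.7; QALY = (u0 + u12)/2. The ratios in steps 1 and 2 do not depend on s.

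**Step 1: no adjustment against adjustment for u0.**
- Unadjusted variance per person: s²(1 + r)/2.
- Variance after regression on u0: s²(1 − r²)/4.
- Ratio of standard errors: √[2/(1 − r)].
- At r = 0.5: unadjusted SE = √(2 × 0.0625 × 0.75 / 224) = 0.0205; adjusted SE = √(2 × 0.0625 × 0.1875 / 224) = 0.0102.

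**Step 2: the article's conditional rule.** Read as a two-sided 5% test of baseline utility, with adjustment only when it is significant (simulation of 200,000 trials).

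**Step 3: deaths.** The article's 10.5% mortality, with month-12 utility set to zero for those who die. Death is taken as unrelated to baseline utility, with assumed mean utility 0.70 at baseline and 0.65 in survivors.

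Each entry is the SE relative to the always-adjusted SE:

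| r | Never adjusted | Adjusted only if flagged at 5% | Never adjusted, deaths as zero |
|---|---|---|---|
| 0.3 | 1.69 | 1.53 | 1.45 |
| 0.5 | 2.00 | 1.78 | 1.60 |
| 0.7 | 2.58 | 2.25 | 1.83 |

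The conditional rule recovers only a small part of the loss.

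**Step 4: what can slip under the flag.** A baseline imbalance at p = 0.10 is 1.645 × 0.25 × √(2/224) = 0.0389 in utility. Half of it, 0.0194 QALY, enters the unadjusted difference directly. With the expected carry-over into month 12 at r = 0.5 it is 0.75 × 0.0389 = 0.029.

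**Step 5: net benefit.** With threshold λ and cost SD c, taking costs as independent of QALYs and leaving cost variance unchanged, the SE ratio is √[(λ² × unadjusted variance + c²) / (λ² × adjusted variance + c²)]. At r = 0.5:
- λ = 100,000, c = 10,000: √(5.69 × 10⁸ / 2.17 × 10⁸) = 1.62.
- λ = 20,000, c = 30,000: √(9.19 × 10⁸ / 9.05 × 10⁸) = 1.01.

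The other combinations tried (λ from 20,000 to 100,000, c from 10,000 to 30,000) lie between these two.

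**Step 6: dependence on the QALY formula.** If the QALY rested on month-12 utility alone, the ratio at r = 0.5 would be 1/√(1 − r²) = 1.15. If it rested on change from baseline, it would be √[2/(1 + r)] = 1.15.

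**The case against.** The strongest reply is that the article is brief on this point and does not actually choose an unadjusted analysis. It never describes the increments as raw differences in means. The Abstract says that intervention effects come from multivariate regression and lists cost-effectiveness among the secondary outcomes, and a fuller economic plan may specify the covariates. A reader might infer that the trial will definitely leave baseline utility unadjusted; the text does not support that. What remains is that the article does state a rule for all subsequent analyses, and that rule lets baseline utility in only after a notable difference. Even the covariate list for the secondary outcomes omits it. A poor rule that is stated is more than a detail left for later.

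Three other stronger readings also fail.
- **That the ICER's uncertainty is about twice what it need be.** The factor of 2 belongs to the QALY difference, at an assumed correlation of 0.5 and with no deaths. Cost variance dilutes it, and no net-benefit setting tried at that correlation reached it.
- **That the result is biased.** Under randomisation the unadjusted difference is unbiased, and the bootstrap interval includes the baseline variation. It is wider than it has to be, not wrong.
- **That baseline utility is part of each QALY as a matter of record.** The article mentions life expectancy and no formula. The two-visit schedule makes the area under the curve the natural reading, but it is an inference, and step 6 shows how much depends on it.

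**Conclusion.** The point stands as a recommendation on efficiency and pre-specification, worth acting on before the economic analysis is fixed. Beyond a data-dependent rule with no stated threshold, the article sets out no adjustment of the incremental QALY for baseline utility, although that value is collected.

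If the QALY is the two-point area under the curve, the cost is an SE of the QALY difference about 1.7 to 2.6 times the adjusted one for correlations of 0.3 to 0.7. Counting the 10.5% deaths as zero utility brings this to about 1.5 to 1.8. Following the conditional rule at a 5% level, without deaths, leaves about 1.5 to 2.3.

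For net benefit and the acceptability curve the gain is smaller and depends on cost variance and threshold: illustratively 1.01 to 1.62 at a correlation of 0.5, before any gain from adjusting costs. The SDs, correlations, thresholds and QALY formula are assumptions, as the article gives none of them.

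**What to change.** In the economic paragraph of {20a}, state the QALY formula and replace reliance on the baseline check with text along these lines:

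> Incremental QALYs will be estimated by regression on treatment arm, adjusted for the respondent's baseline EQ-5D-5L utility and for memory clinic. Incremental costs will be estimated by regression on treatment arm, adjusted for baseline FIMA/RUD costs and for memory clinic. These adjustments will be made whatever the baseline comparison shows. In each bootstrap sample, dyads will be resampled within arm and clinic, both models refitted, and the ICER and the probabilities of cost-effectiveness formed from the adjusted increments. The unadjusted ICER will be reported as a sensitivity analysis.

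Apply this to patient and caregiver QALYs alike. If a separate economic plan already says this, one clause in the article is enough.

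The cost is wording and a few lines of code. Baseline utility is already collected, and so are baseline resource-use data if the stated two-visit schedule covers FIMA and RUD, as I read it. No extra participants, visits or staff are needed.
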